### Objectives

The primary objective of this study is to establish the acceptability, feasibility, and other implementation challenges of the eCDSS (CogStack@Maudsley), comprising a real-time computerized alerting and clinical decision support system, in supporting dysglycemia management in an inpatient secondary mental health care setting.

Our secondary objective is to assess the change in rates of guideline-indicated tests or interventions for dysglycemia on the test wards before and after the introduction of the eCDSS, compared to comparator wards without access to the eCDSS.

This will be measured using pseudonymized group observational data gathered from the South London and Maudsley NHS Foundation Trust Biomedical Research Centre’s Clinical Records Interactive Search (CRIS) system. Since 2006, the South London and Maudsley NHS Trust has operated fully electronic health records. The CRIS system, established in 2008, is an ethically approved electronic health records interface system that allows researchers to access deidentified electronic health records from this trust for research purposes [24-26].

Data gathered from this study will allow us to refine the system, address potential challenges with future successful implementation, and inform a larger and more definitive effectiveness trial that will examine for hypothesized improvements in (1) rates of clinician-delivered, evidence-based interventions for patients with dysglycemia and (2) clinical outcomes relating to diabetes care.

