### Randomization

Wards will be the unit of recruitment and will be assigned randomly to either the intervention or TAU group to receive either the eCDSS platform alongside usual care or to follow usual care processes only for a period of 4 months. We will recruit and randomly allocate 2 wards to the intervention arm and 3 wards to the comparator arm using fixed block randomization. Random allocation of the wards will be done by an independent trial manager who is outside of the research team to ensure there is no bias in allocations.

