### Intervention

We previously developed an eCDSS for dysglycemia hosted within CogStack@Maudsley [23]. The eCDSS is designed to alert clinicians automatically when patients are admitted under their care regarding the need for screening for, or management of, dysglycemia. Prompts are triggered by the presence of new, old, or absent HbA_1c_ pathology reports in the electronic health record.

Digital-enabled clinical decision support is provided as a combination of visual prompts on a dashboard embedded within an existing electronic platform used at the NHS Trust and email supplements sent to NHS Trust email accounts of participating wards. The eCDSS was designed to integrate as easily as possible within existing workflows by building it into the existing NHS Trust electronic systems that clinicians use in inpatient wards.

The alerts in this study will include NHS Trust “Quality Centre”–approved, guideline-based recommendations for clinician-led monitoring and management of dysglycemia and known diabetes, tailored to the individual patient’s reported HbA_1c_ values. The eCDSS algorithm is based on gold-standard clinical management guidelines, which were developed and agreed upon by the NHS Trust [23].

Clinicians on intervention wards will be able to view priority-tagged prompts in the EHR system, corresponding to guideline-based recommended actions they can access for further patient-specific guidance with regard to their care. Clinicians are already familiar with the platform for other uses, but a demonstration of the system will be given to users before the intervention period, so they are aware of how the system is accessed and used. Access to the system will be restricted to the intervention wards only, but access to it can be expanded in the future to more wards and teams.

The research team will be available to provide support to clinicians participating in the study to ensure that any technical queries relating to the eCDSS are dealt with appropriately. The research team will also work closely with the host trust IT department so that any potential technical issues are responded to quickly.

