**Secondary outcomes (processes of care)**					
	HbA_1c_^b^ testing	Rates of HbA_1c_ testing on inpatients		Quantitative	
	Documentation of dysglycemia or diabetes in clinical notes	Documentation of diabetes or prediabetes diagnosis in case notes during inpatient stay (where indicated)		Quantitative	
	Documentation of discussion with patient regarding exercise, diet, and smoking cessation	Documentation of advice by clinician given to the patient regarding lifestyle changes—exercise, diet, and smoking cessation in patients with dysglycemia		Quantitative	
	Documentation of diabetes-related screening interventions	Documentation of completed foot check for patients with diabetes		Quantitative	
	Delivery of evidence-based pharmacological interventions for diabetes or prediabetes where clinically indicated	Documentation of discussion regarding diabetes-related medication changes post alerting where clinically indicated: Initiation of diabetes-related medication Intensification of medication (dose change or introduction of new agent in accordance with guidance)		Quantitative	
	Communication with general practitioner or community mental health team regarding diabetes or dysglycemia follow-up	Documentation to relevant community teams and GP^c^ regarding follow-up plans for dysglycemia management post discharge where indicated		Quantitative	

^a^eCDSS: electronic clinical decision support system.

^b^HbA_1c_: glycated hemoglobin.

^c^GP: general practitioner.

A process evaluation of the implementation of the intervention will be conducted to identify factors that inhibit or facilitate implementation. A mixed methods approach will be adopted to establish feasibility, acceptability, and other implementation outcomes.

Details of the study were first shared among ward managers and consultants in January 2022, and formal enrollment of eligible wards began in April 2022. Clinical staff on recruited wards were then individually recruited to take part in surveys and interviews starting in June 2022. The intervention period of the trial began in February 2023, and qualitative data collection was completed in August 2023. All interviews were recorded and subsequently transcribed verbatim.

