### Analysis

Mixed methods will be used to analyze the outcome data generated.

Qualitative analysis of data generated through semistructured interviews and surveys of clinician users will be used to evaluate the primary outcome measures relating to implementation. A thematic analysis of interview transcripts will be conducted. We will then use a qualitative process evaluation, grounded within established implementation science frameworks, to analyze and report on the implementation outcomes generated [28-30].

We will compare changes in the process of care measures between intervention and control groups to evaluate the eCDSS impact on the process of care measures by analyzing group-level pseudonymized observational data through the CRIS platform. Descriptive statistics will be used to report on these results.

Key stakeholders will be informed of the outcomes of the study through internal report and the presentation of the study results at local meetings. It is planned that the methods and findings of the study will be incorporated into an original research paper that can be widely shared, following peer review in a journal.

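### The pharmacological process outcome is tied to an alert that comparator wards and the pre-period do not have, so as worded it cannot enter the planned between-arm comparison of change

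*Protocol article*

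**What the plan says.** In the protocol article, Table 1 lists six process-of-care outcomes as secondary outcomes. One is labelled "Delivery of evidence-based pharmacological interventions for diabetes or prediabetes where clinically indicated". Its definition begins "Documentation of discussion regarding diabetes-related medication changes post alerting where clinically indicated" and then, after a colon, names two kinds of change: starting a diabetes-related drug, and intensifying treatment by a dose change or a new agent.

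The Intervention section states "Access to the system will be restricted to the intervention wards only". The Randomization section says the trial will "randomly allocate 2 wards to the intervention arm and 3 wards to the comparator arm". The text after Table 1 dates the start: "The intervention period of the trial began in February 2023".

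The secondary objective concerns change in rates of guideline-indicated tests or interventions "on the test wards before and after the introduction of the eCDSS, compared to comparator wards without access to the eCDSS". The Analysis section repeats the contrast: "We will compare changes in the process of care measures between intervention and control groups". It covers the process measures as a group, does not set the pharmacological row apart, and says that reporting will be descriptive.

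**The concern.** A rate compared between arms and over time needs a numerator and a denominator that mean the same thing in every cell of the comparison. This outcome counts only events that follow an alert, and an alert is part of the intervention. Comparator wards never have one, and no ward has one before go-live. The definition therefore conflicts with the analysis it is meant to feed.

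At stake is the only medication measure among the process outcomes. The Objectives section says the study's data will inform a later definitive trial, which will look for improvement in clinician-delivered, evidence-based interventions. A medication measure that exists only in the intervention arm after go-live gives that trial no comparator rate and no baseline rate.

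**Working it through.** The plan gives no sample size, power or target rate for this outcome, so there is no stated figure to reproduce. The check is a count of the cells in which the definition can be applied.

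**Inputs**
- Wards: 2 intervention and 3 comparator, 5 in total (Randomization).
- Periods: 2, before and after the system is introduced (Objectives).
- Alerts: intervention wards only (Intervention), from February 2023 (text after Table 1).
- Condition in the outcome: the discussion must follow an alert (Table 1).

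**Arm-by-period cells:** 2 arms × 2 periods = 4.

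| | Before | After |
|---|---|---|
| Intervention | no alert, not defined | alert, defined |
| Comparator | no alert, not defined | no alert, not defined |

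Defined: 1 of 4.

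**Ward-by-period cells:** 5 × 2 = 10.
- Defined: 2 intervention wards × 1 period = 2.
- Not defined: 2 (intervention, before) + 3 (comparator, before) + 3 (comparator, after) = 8.

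**Consequence for each possible contrast**
- Difference in change = (intervention after − intervention before) − (comparator after − comparator before). Three of its four terms are not defined.
- Post-period difference = intervention after − comparator after. The second term is not defined.
- Change within the intervention arm = intervention after − intervention before. The second term is not defined.

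**Comparison with the other rows.** None of the other five process outcomes in Table 1 depends on an alert. The row on recording a diagnosis in the notes uses the inpatient stay as its window, which exists in every ward and both periods. The problem is confined to this one row.

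**The case against.** **The data may allow it.** The Intervention section says "Prompts are triggered by the presence of new, old, or absent HbA_1c_ pathology reports in the electronic health record". HbA1c reports exist on every ward, and Baseline Measurements plans to request HbA1c levels from CRIS. A reader might infer from the Table 1 wording that the outcome can never be obtained for comparator wards. The documents do not support that: an equivalent trigger might be reconstructed. What stands against the plan is narrower. The article describes no silent run of the algorithm and no substitute index event, and its wording requires an alert.

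**An article leaves detail to the full protocol.** This is fair for the exact window and denominator, and their absence is no finding. The alert condition is different. It is a stated definition that conflicts with the stated objective and analysis.

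**Emails go to participating wards.** The Intervention section uses that term for the email recipients, and Recruitment and Eligibility uses it for all five wards. The explicit restriction of access, and the description of comparators as having no access, make intervention-only alerting the sound reading.

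**Delivery and discussion.** A reader might infer that a discussion ending in no change scores as delivery, so that treatment is overstated. The definition goes on to list initiation and intensification, which may specify what has to happen. The text is ambiguous and does not establish the stronger reading.

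**Bias.** A reader might also infer a biased contrast, with events after an alert counted in one arm and events at any time in the stay in the other. No section proposes that analysis, so the bias is hypothetical.

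**Importance.** The primary outcomes are implementation outcomes, no power analysis was done for intervention effects, and reporting is descriptive. This objection stands and limits the weight of the point.

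**Conclusion.** The point holds in this form: the alert condition in the pharmacological row of Table 1 is incompatible with the before-and-after, between-arm comparison in the Objectives and Analysis sections. As worded, the outcome is defined in 1 of 4 arm-by-period cells (2 of 10 by ward). This rests on two readings: that alerting took text in its plain sense means an eCDSS alert, and that no ward received alerts before February 2023.

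The cell count shows how much of the comparison lacks a definition. It does not measure an effect on any result. The impact is modest: one of six secondary outcomes, in an unpowered pilot with descriptive reporting, and the other five rows are unaffected. The mismatch between label and definition is a secondary point that needs clarification. It is not evidence that delivery is overstated.

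**What to change.** 1. Delete the alert condition from this row. Measure the outcome over the inpatient stay, in patients for whom it is clinically indicated, with the same denominator and window in all five wards and both periods.
2. Alternatively, if the CRIS extract and its approval allow the event to be dated, anchor the outcome to the qualifying HbA1c result, or to admission where a result is already on file. Apply the anchor identically everywhere.
3. State whether the row scores a documented discussion or a recorded initiation or intensification. Preferably report the two as separate measures, and keep the delivery label for the second.

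The first and third changes are edits to the wording of Table 1, although reporting two measures needs both to be extractable from the records. The second may cost more. The article plans group-level data, says that individual patient outcomes will not be recorded, and makes data access subject to the CRIS oversight committee. It does not show that dated, patient-level triggers are covered. The first change has a small downside: on intervention wards the measure may include discussions held before the alert. The article says analysis is under way, so the definition should be settled and recorded before this row is reported.

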### Baseline Measurements

We will collect the following sociodemographic data on participating clinicians from recruited wards: age, gender, years of clinical experience, specialty or profession, and grade.

No identifiable data will be collected on patients on the recruited wards. However, a separate application will be made to the CRIS oversight committee to gather the following pseudonymized information at a ward or group level: age, gender, ethnicity, HbA_1c_ levels, recorded history of diabetes, International Classification of Diseases-10th revision (ICD-10) mental disorder diagnosis, and history of referral to diabetes specialist teams.

### Analysis

Mixed methods will be used to analyze the outcome data generated.

Qualitative analysis of data generated through semistructured interviews and surveys of clinician users will be used to evaluate the primary outcome measures relating to implementation. A thematic analysis of interview transcripts will be conducted. We will then use a qualitative process evaluation, grounded within established implementation science frameworks, to analyze and report on the implementation outcomes generated [28-30].

We will compare changes in the process of care measures between intervention and control groups to evaluate the eCDSS impact on the process of care measures by analyzing group-level pseudonymized observational data through the CRIS platform. Descriptive statistics will be used to report on these results.

Key stakeholders will be informed of the outcomes of the study through internal report and the presentation of the study results at local meetings. It is planned that the methods and findings of the study will be incorporated into an original research paper that can be widely shared, following peer review in a journal.

## Results

As this paper is a study protocol, no results are currently available. Enrollment of wards began in April 2022, after which clinical staff were recruited to take part in preintervention surveys and interviews. The intervention period of the trial began in February 2023, and subsequent data collection for postintervention interviews and surveys was completed in August 2023. Data are currently being analyzed, and results are expected to be available in June 2024.

## Discussion

### Overview

To our knowledge, this will be the first-ever trial of an eCDSS comprising an automated electronic physical health monitoring and alerting platform developed for use in a secondary care mental health setting, which aims to improve the clinician-led management of dysglycemia and diabetes care to patients with SMI. eCDSS has the potential to radically improve the standards of physical health care offered to patients with SMI and may be a crucial step in reducing the morbidity and mortality associated with chronic physical health conditions in SMI.

Implementation of eCDSS for use in clinical settings has previously been shown to be time-consuming, and its complexity can result in slow adoption into practice [20]. To bridge this gap, we have adopted a stepwise approach, starting with technical development and in silico evaluation [23], and progressing to this pilot, with the aim of informing further refinement, development, and engineering of the eCDSS, to enable its longer-term successful adoption in clinical practice.

Integration of eCDSS into existing clinical workflows is not simple, and digital health systems that are not wholly accepted by their users cannot be expected to contribute to improving care, hence the need for research into facilitators and barriers to adoption. These need to be well understood to support the successful implementation of novel digital tools, with calls for research to include evaluating eCDSS implementation for successful future scalability [22].

Gaining a good understanding of the factors that affect the adoption and integration of digital health tools into routine practice could also serve as a basis for creating frameworks for delivering future impactful digital tools. For this reason, we have included implementation outcomes alongside other measures of effectiveness, to inform further work that aims to facilitate smoother implementation of digital technologies into clinical settings. This knowledge can then be used to apply and scale the eCDSS for other physical health conditions in SMI, such as atrial fibrillation, hypertension, and hypercholesterolemia.

This study does have some limitations. Recruitment is limited to 1 NHS Trust, with 2 wards allocated to the intervention arm from 1 site, thus limiting the extent to which broader conclusions can be made as the findings are not generalizable. There could be a self-selection bias in regard to staff who agree to participate in interviews and surveys, as it is possible that they are more likely to be interested in or accustomed to novel digital technologies. All staff will be encouraged to ask the research team about any concerns they may have so that they can be addressed with a view to reducing the risk of this. It is possible that different data might be generated if it were conducted in settings across multiple sites. Given the study design, there is also the possibility of the Hawthorne effect, which is well documented in research, when participants may knowingly or unknowingly alter their behaviors as a result of being observed as part of the study [28]. Nonetheless, this pilot study still serves as a useful basis for preliminary research in a setting that has not been explored in depth previously.

We have previously demonstrated that it is technically feasible to design and deploy a functional monitoring and alerting eCDSS for dysglycemia in a secondary care setting for mental health [23]. This pilot feasibility trial seeks to further improve our understanding of the implementation challenges of implementing a new digital system that aims to improve physical health care provision to patients in mental health settings and inform a further, more comprehensive evaluation of the eCDSS. Key implementation outcomes, including acceptability and feasibility, will be evaluated alongside outcomes relating to impacts on care processes and based on established implementation science methods [29-31].

### Conclusion

An eCDSS can have the potential to improve clinician-led management of dysglycemia in inpatient mental health settings. If found to be feasible and acceptable in this study, then, in combination with the results of the implementation evaluation, the system can be refined and improved to support future successful implementation. A larger and more definitive effectiveness trial should then be conducted to assess its impact on clinical outcomes over a longer period of time and to guide its scalability and application to other conditions in wider mental health care settings.

## Abbreviations

CRIS: Clinical Records Interactive Search
CVD: cardiovascular disease
eCDSS: electronic clinical decision support system
ICD-10: International Classification of Disease-10th revision
NHS: National Health Service
SMI: severe mental illness
TAU: treatment as usual
